**Objective:**

The aim of this pilot randomized controlled trial (RCT; the VISTA-JIA trial) is to evaluate the feasibility and preliminary effectiveness of a virtual group-based SMP for adolescents with JIA in comparison to a waitlist control group.

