**Methods:**

A total of 100 participants with confirmed JIA (aged 12-17 years) will be recruited from 5 Canadian pediatric rheumatology centers and randomized 1:1 to the intervention or waitlist control groups. Adolescents in the intervention group will receive the virtual SMP. Those randomized to the control group will receive standard of care alone and will later be eligible for the SMP. The SMP includes JIA disease education, self-management strategies, and peer support. Four 60- to 90-minute sessions will be conducted over 8 weeks with a group size of 4-6 participants. The primary feasibility outcome will be adherence to the SMP (defined as completion of all 4 sessions by at least 80% of participants). Other secondary feasibility outcomes will include recruitment and withdrawal rates, the proportion of completed questionnaires, engagement and satisfaction with the SMP measured through a semistructured virtual interview, and intervention fidelity (consistent content and technology delivery). Secondary preliminary effectiveness outcomes will be assessed by completing 5 validated questionnaires at pre- and postprogram time points: (1) the Medical Issues, Exercise, Pain, and Social Support Questionnaire to assess perceived ability to manage JIA (self-management); (2) the Children’s Arthritis Self-Efficacy Scale to assess self-efficacy; (3) the Pediatric Quality of Life Inventory 3.0 Rheumatology–Teen Module to assess health-related quality of life; (4) the PROMIS (Patient-Reported Outcomes Measurement Information System) Pediatric Pain Interference Scale to assess pain interference; and (5) Readiness for Adult Care in Rheumatology to assess transition readiness. Descriptive statistics and nonparametric tests will be used to analyze the data.

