## Methods

### Study Design

A pilot RCT will be conducted to determine the feasibility and preliminary effectiveness of a virtual SMP intervention. Eligible participants will be randomized 1:1 to either the intervention group or a waitlist control group. Both groups will complete baseline measures (T0) as well as postprogram measures (T1). Participants enrolled into the intervention will undergo the SMP and be asked to participate in an optional postintervention interview. The waitlist control group will continue receiving standard of care during this program period. They will be given the option to complete the SMP afterwards, and if completed, be asked to complete postintervention questionnaires. They will also be asked to participate in the optional postintervention interview. The study is registered in ClinicalTrials.gov (NCT06184100). Figure 1 shows the trial schema, and Multimedia Appendix 1 shows the timeline. This study follows the SPIRIT (Standard Protocol Items: Recommendations for Interventional Trials; checklist provided in Multimedia Appendix 2) guidelines.

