##### Preliminary Effectiveness Outcomes

The quantitative data will be entered into SPSS [34]. Descriptive statistics will be used to analyze the patient-reported outcome measures with an ordinal Likert scale at baseline and immediately post intervention. In addition, nonparametric Wilcoxon signed rank tests will be used to assess if there is a significant difference between a pre- and posttest outcome. Nonparametric tests will be used due to the small sample size and a lack of normally distributed data. Changes in pre- and posttest outcomes will be analyzed over time using a repeated measures mixed linear model approach where participants will be included as the random effect and baseline scores, study site, and disease-related characteristics will be used as fixed factors or covariates.

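### The effectiveness analysis specifies no comparison of the programme with waitlist: its named test is pre/post and the model's listed terms omit randomised arm

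*Protocol article*

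**What the plan says.** The Objective in the abstract of the protocol article is to "evaluate the feasibility and preliminary effectiveness of a virtual group-based SMP for adolescents with JIA in comparison to a waitlist control group". The aim at the end of the Introduction repeats this. Under Study Design, "Eligible participants will be randomized 1:1 to either the intervention group or a waitlist control group", and both arms complete the questionnaires at T0 and T1.

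The Preliminary Effectiveness Outcomes section then gives three pieces of analysis:

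- descriptive statistics at baseline and after the intervention;
- a paired test: "nonparametric Wilcoxon signed rank tests will be used to assess if there is a significant difference between a pre- and posttest outcome";
- a model: "Changes in pre- and posttest outcomes will be analyzed over time using a repeated measures mixed linear model approach", in which "participants will be included as the random effect and baseline scores, study site, and disease-related characteristics will be used as fixed factors or covariates".

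The Methods part of the abstract sums this up as "Descriptive statistics and nonparametric tests will be used to analyze the data". The signed rank test is the only nonparametric test that the article names.

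**The concern.** The objective asks whether adolescents given the SMP do better than those on the waitlist. A signed rank test on pre/post pairs asks whether scores changed within people. These are different questions, and the second needs no control arm. The mixed model could answer the first, but the terms listed for it do not include the one that would do so.

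Scores can change without the programme. Both arms continue under standard of care, and both fill in the same self-reported questionnaires twice. A pre/post test cannot separate such common change from an effect of the SMP; the difference between the randomised arms can. The pilot's results are meant to inform a full-scale trial, so an uncontrolled change reported as the effectiveness result would be a poor planning figure.

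**Working it through.** **The plan's own figure.** Two offerings at each of 5 sites with groups of 4 to 6 give 2 × 5 × 4 = 40 to 2 × 5 × 6 = 60 in the SMP arm. The midpoint, 2 × 5 × 5 = 50, and 1:1 allocation reproduce the stated 50 + 50 = 100. The article gives no alpha, effect size, SD or pre-post correlation, so everything numerical below rests on assumptions.

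**The text, item by item.**

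| Planned item | Question it answers | Is arm named? |
|---|---|---|
| Descriptive statistics at both times | Level of scores | No |
| Wilcoxon signed rank | Did scores change within people? | No; a paired test cannot contrast independent arms |
| Mixed model over time | Change over time, given the listed terms | No arm or arm-by-time term listed |
| Subgroup interaction tests | Does effectiveness differ by site or patient characteristic? | No; arm may be implied |
| Intention to treat (missing data section) | Which participants are analysed | No contrast given |

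**Illustration of the consequence.** Assumptions: 50 per arm, normal scores with SD 1, independent participants, no SMP effect, the same pre-to-post shift in both arms, correlation ρ between T0 and T1, two-sided 5%. Percentage of 3,000 simulated trials with a significant result:

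| Common shift (SD) | ρ | Signed rank, SMP arm (n = 50) | Signed rank, arms pooled (n = 100) | Arm term, T1 adjusted for T0 |
|---|---|---|---|---|
| 0 | 0.5 | 4.8 | 5.4 | 4.8 |
| 0 | 0.7 | 5.0 | 5.3 | 4.5 |
| 0.2 | 0.5 | 27.2 | 48.9 | 5.0 |
| 0.2 | 0.7 | 41.4 | 70.7 | 4.8 |
| 0.3 | 0.5 | 52.6 | 81.1 | 5.7 |
| 0.3 | 0.7 | 73.9 | 96.2 | 4.6 |
| 0.4 | 0.5 | 77.1 | 97.5 | 5.3 |
| 0.4 | 0.7 | 93.8 | 99.8 | 4.5 |

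Both signed rank columns are shown because the article does not say whether the test is run by arm or on everyone. A separate run of 2,000 trials per cell gives 26/41%, 52/73% and 78/94% for the SMP arm at shifts of 0.2, 0.3 and 0.4 SD, hence the range of about 26% to 94%.

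Analytic check with the paired t test: the SD of change is √(2(1 − ρ)), which is 1.00 at ρ = 0.5 and 0.775 at ρ = 0.7. For a shift of 0.2 the noncentrality is 0.2 × √50 / 1.00 = 1.41 or 0.2 × √50 / 0.775 = 1.83, giving power of 0.28 or 0.43, close to the simulated 27% and 41%.

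**A model with time but no arm.** If the listed terms are the whole model apart from time, then with equal arms the time effect is ½(trend + effect) + ½(trend) = trend + effect/2. A true effect of 0.4 SD with no trend would appear as 0.2 SD, and could not be told apart from a trend of 0.2 SD.

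**What the planned data give once arm is named.** For T1 adjusted for T0, the 95% half-width is 1.96 × √(1 − ρ²) × √(2/50):

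- ρ = 0.5: 1.96 × 0.866 × 0.2 = 0.34 SD
- ρ = 0.7: 1.96 × 0.714 × 0.2 = 0.28 SD

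The contrast can therefore be estimated from data already being collected. These widths ignore delivery of the SMP in groups of 4 to 6; correlation within groups would widen them.

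**The case against.** The best defence is that the article condenses a fuller plan. Its list of fixed factors or covariates is not said to be complete, and time is not on the list either, though the same sentence says that change is analysed over time. The Subgroup Analysis section plans interaction tests of the intervention's effectiveness, which in a randomised trial would normally contain an arm term. The authors may well intend one. This stands in part. A reader might infer that the between-arm effect will never be estimated; the text supports only that it is not specified. It is still more than omitted detail, because the article chooses a test, lists model terms, and leaves out the one that its objective requires. The subgroup tests concern effect modification, not the overall difference.

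Second, effectiveness is secondary and preliminary here. Adherence is primary, and the larger trial is made conditional on the programme being feasible and acceptable. This stands and limits the reach of the point. It would go too far to say that randomisation serves no purpose: questionnaire completion, for example, is assessed in both groups.

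Third, some further inferences are tempting but unsupported:

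- Regression to the mean is a weak explanation, because eligibility sets no score or disease-activity threshold.
- Study Design describes the waitlist arm's later questionnaires, after its optional SMP, separately from T0 and T1. Nothing says that they would enter the pre/post test.
- Nowhere does the article propose to claim benefit because the SMP arm is significant and the waitlist arm is not.
- Nowhere does it say that the full-scale trial will be sized on a pre/post change.

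Fourth, the shifts and correlations have no source in the article. That is correct. With no common shift, the signed rank test holds its 5% level.

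**Conclusion.** The point holds: as written, no analysis of the preliminary effectiveness outcomes compares the SMP with waitlist, although that is the stated objective and the data for it are collected in both arms. The size depends on how much scores change for reasons shared by both arms. Under the assumptions above, a pre/post test in the SMP arm would be significant in about 26% to 94% of trials of an ineffective programme for shifts of 0.2 to 0.4 SD, against about 5% for a test of arm; at zero shift there is no inflation. These rates illustrate the mechanism and do not forecast this trial. The 5% for the arm test also assumes independent participants and T0 scores unaffected by allocation. Neither is assured, since the SMP is delivered in groups and randomisation precedes the baseline questionnaires. The primary adherence outcome is not affected.

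**What to change.** In the Preliminary Effectiveness Outcomes section, name randomised arm as the effect of interest for each of the five questionnaires, in one of two forms:

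- T1 score on arm, adjusted for T0 score and site; or
- the planned mixed model with T0 and T1 as outcomes and an arm-by-time term.

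Choose one. T0 should not be both a repeated outcome and a covariate: with two time points, using it as the covariate leaves one outcome per person, and a participant random effect cannot then be separated from residual error.

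Analyse participants as randomised. Report the SMP-minus-waitlist difference with its 95% CI as the effectiveness estimate, and give within-arm pre/post change descriptively only. State that T0 is collected after randomisation, and check how sensitive the CI is to clustering by SMP group. Bring the summary in the abstract into line.

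The cost is a few lines of text and a sensitivity analysis, with no new data, visits or participants. The article reports 40 of 100 enrolled by March 2025, recruitment to December 2025 and analysis after the intervention, so on that timeline the change can be made before the data are analysed.

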### Randomization, Recruitment, and Sample Size

CONSORT (Consolidated Standards of Reporting Trials; checklist provided in Multimedia Appendix 3) 2010 guidelines suggest a sample size calculation of 9% of the anticipated full-scale RCT for the intervention group in pilot studies [22,23]. However, to establish feasibility at several sites and get an estimate of a statistically significant SD to inform a full-scale multicenter trial, our target is to conduct 2 offerings of the program with 4-6 participants per group at each of the 5 sites to control for site-specific education. Eligible participants will be identified through a review of the patient database and will be contacted by research coordinators. Some participants will also be recruited during their clinic visits. They will receive detailed information about the study, including its objectives, procedures, and potential benefits. Interested participants will provide informed consent (or assent, with parental consent for minors). The study aims to recruit a total of 100 participants. Therefore, we will require 50 participants in the intervention group and 50 in the waitlist control group. This sample size was chosen to establish feasibility and inform a larger multicenter trial. Participants will be randomized 1:1 to either the intervention group or the waitlist control group using block randomization with variable block sizes. This randomization will be conducted using REDCap (Research Electronic Data Capture; Vanderbilt University), a secure web-based application for managing data. Randomization will occur before baseline measures are completed. Participants in the intervention groups will be from the same center to adapt the program to local health care systems and account for the variability of nonformal educational practices between centers. This approach will also facilitate an evaluation/subgroup analysis of outcome measures at each center.

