### Intervention

The program consists of JIA disease education, self-management strategies, and peer support in a group-based setting. Four sessions, 60-90 minutes each, will be conducted over 8 weeks with a group size of 4-6 participants via videoconferencing platforms. Each session will include Microsoft PowerPoint–delivered presentations, interactive activities, and group discussions. The 4 sessions will focus on the following themes: Overview and Diagnosis of JIA, Daily Living and Exercise, Coping Strategies, and Medication and Lifestyle Management. To ensure intervention fidelity, sessions will be provided by the same designated health care professionals. All sessions will be video-recorded and uploaded to a secured research server to assess the group’s dynamic and ensure sessions are delivered as planned (fidelity). Young adults living with JIA from participating centers will be asked to sit in during these sessions to share their lived experiences and foster peer social support. Additionally, each site will include site-specific resources. After completing the intervention, participants will be asked to independently attend an optional semistructured interview to capture participant experiences of the intervention.

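### The SMP is given in about 10 single-center groups, but the mixed model's only stated random effect is the participant; if outcomes correlate within groups, between-arm standard errors are modestly too small

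*Protocol article*

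**What the plan says.** All references are to the protocol article.

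- **Randomization, Recruitment, and Sample Size.** Allocation is individual: "Participants will be randomized 1:1 to either the intervention group or the waitlist control group using block randomization with variable block sizes". The target for delivery is given as "our target is to conduct 2 offerings of the program with 4-6 participants per group at each of the 5 sites", and for numbers as "we will require 50 participants in the intervention group and 50 in the waitlist control group". On the make-up of groups: "Participants in the intervention groups will be from the same center". The only variance quantity that the pilot is said to supply to the larger trial is an SD.
- **Intervention.** "Four sessions, 60-90 minutes each, will be conducted over 8 weeks with a group size of 4-6 participants via videoconferencing platforms". The same section assigns the same designated professionals to the sessions and brings in young adults with JIA as peers.
- **Study Design.** "The waitlist control group will continue receiving standard of care during this program period", so controls belong to no SMP group while the randomized comparison runs.
- **Preliminary Effectiveness Outcomes.** The repeated measures mixed model is one "where participants will be included as the random effect". Baseline score, study site and disease characteristics enter as fixed factors or covariates. No SMP-group term, cluster-robust variance or ICC appears there or elsewhere in the article.

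**The concern.** This is an individually randomized trial with grouping in one arm only (partial nesting). Members of one SMP group share facilitators, peers, guests and session dates. The Introduction and the Significance section present learning from and supporting one another as part of how the program works. Outcomes after the program may therefore be more alike within a group than between groups.

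A participant random effect handles repeated measures on one person. It says nothing about correlation between different people in the same group. Study site as a fixed term removes differences between centers that both arms share. It does not remove a difference between the two offerings at one center, or an effect present only in the SMP arm.

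Two things are at stake. Precision for a between-arm effect would be somewhat overstated. And the pilot, which is meant to inform a larger trial of a group-delivered program, would not report the group-level correlation that such a trial has to allow for.

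**Working it through.** **Inputs from the article.** 5 sites, 2 offerings per site, 4-6 participants per group, 50 per arm, 1:1 individual allocation, ungrouped controls.

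**Assumed.** The ICC within SMP groups, conditional on the model's covariates. The article gives none, so a range of 0.01 to 0.20 is shown.

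**1. The plan's own figure.** 5 sites × 2 offerings × 5 participants (midpoint of 4-6) = 50 in the SMP arm; doubled for 1:1 allocation = 100. This matches the stated target. Groups of 4 would give 80 and groups of 6 would give 120. The number of SMP groups is 5 × 2 = 10.

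**2. Effect on a between-arm standard error.** With mean group size m:

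- design effect in the SMP arm: DE = 1 + (m − 1) × ICC
- true over naive variance of the arm difference, with only one of two equal arms clustered: R = (DE + 1)/2
- understatement of the standard error: 1 − 1/√R
- actual level of a nominal two-sided 5% test: 2 × [1 − Φ(1.96/√R)]

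Example, m = 5 and ICC = 0.05: DE = 1 + 4 × 0.05 = 1.20; R = 2.20/2 = 1.10; √R = 1.049; understatement 4.7%; actual level 6.2%.

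| ICC (assumed), m = 5 | DE | R | SE too small by | Actual level |
|---|---|---|---|---|
| 0.01 | 1.04 | 1.02 | 1.0% | 5.2% |
| 0.05 | 1.20 | 1.10 | 4.7% | 6.2% |
| 0.10 | 1.40 | 1.20 | 8.7% | 7.4% |
| 0.20 | 1.80 | 1.40 | 15.5% | 9.8% |

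Across the stated group sizes, the understatement at ICC 0.05 is 3.6% (m = 4) to 5.7% (m = 6), and at ICC 0.10 it is 6.7% to 10.6%.

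**3. Does the fixed site term cure it?** A simulation (8,000 runs per ICC) used 5 sites, 2 groups of 5 per site and 50 ungrouped controls. The analysis model had arm, baseline score and fixed site. With one follow-up score and baseline as a covariate, this stands in for the stated mixed model.

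| ICC | True SE | Mean model SE | Type I error |
|---|---|---|---|
| 0 | 0.200 | 0.200 | 4.9% |
| 0.05 | 0.210 | 0.200 | 5.9% |
| 0.10 | 0.219 | 0.199 | 7.5% |
| 0.20 | 0.235 | 0.198 | 9.6% |

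The model is right when there is no clustering, and the shortfall remains with site fitted when there is.

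**4. How well can 10 groups estimate the ICC?** At a true ICC of 0.05, the central 95% of simulated estimates ran from about −0.15 to 0.29. For the one-way ANOVA estimator, the estimate is zero or negative when F falls below (1 − ICC)/(1 + 4 × ICC) = 0.95/1.20 = 0.79, on the scale of a central F. That has probability 37% with 9 and 40 degrees of freedom, and 44% with 5 and 40 once site is fitted.

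**5. Relevance to a full trial (illustration only).** For an assumed effect of 0.4 SD, 80% power and two-sided 5%, about 99 per arm are needed without clustering. Multiplying by R for groups of 5 gives 103, 109 and 119 per arm at ICC 0.02, 0.05 and 0.10.

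**The case against.** The strongest reply has five parts.

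- **The size rests on an assumed ICC and is modest.** This stands. If the ICC is zero the stated model is correct, and at 0.01 nothing of practical weight is lost. Effectiveness is a secondary, preliminary aim, and no stated decision turns on a p-value near 0.05.
- **The article states no between-arm test, alpha or interval, and the model sentence names no arm term.** This stands as a limit on wording. The figures above apply to any between-arm effect taken from the model. They do not correct a reported figure.
- **Adherence.** A reader might infer that the interval for the primary adherence proportion is also too narrow. The document does not support that: the Data Analysis Plan treats feasibility outcomes descriptively and plans no adherence interval. Clustering does not in itself bias the observed proportion. Only if an interval were added would it need to allow for groups.
- **The full-scale trial.** A reader might infer that a trial sized from this pilot must be too small. That does not follow. Nothing says that the later trial will ignore clustering or take its ICC only from here. External values could be used, and the pilot's own ICC would be very uncertain.
- **This is a condensed article with no analysis plan shown, and site interactions are planned.** This does not remove the point. The article itself states the random-effects structure, and that structure does not fit the delivery. The interaction tests by site under Subgroup Analysis address variation in effect between centers, but not between the two offerings at one center.

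**Conclusion.** The point holds in a limited form. As stated, the mixed model leaves out a plausible source of correlation in the SMP arm, and neither the participant effect nor the site term replaces it. If the within-group ICC is positive, between-arm standard errors from this model are too small by about 5% at an ICC of 0.05 and 9% at 0.10 with groups of 5, and by about 1% at 0.01. These sizes rest on an ICC that the documents do not give, on about 10 groups of near-equal size, and on an arm effect being estimated from this model. The direction is well supported by the design; the size is uncertain and probably modest. It is worth correcting because the correction is cheap and because group-level correlation is relevant to a pilot for a group-delivered program. It does not undermine the feasibility aims.

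**What to change.** 1. Record which SMP group each intervention participant was assigned to.
2. Replace the random-effects wording with a partially nested model: a random SMP-group effect in the intervention arm only, each waitlist participant treated as a singleton cluster, the participant effect kept where repeated measures are modeled, and a small-sample degrees-of-freedom method suited to about 10 groups.
3. Report the group ICC for each outcome with its confidence interval, as one input to sizing the full-scale trial, and say that it will be read together with external ICC values.
4. If an interval is ever placed around the adherence proportion, allow for grouping there too.

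**Cost.** Analysis wording and one group-identifier variable; no change to conduct or sample size. As of March 2025 the article reports 40 participants enrolled and one education intervention conducted, so the change can still be made before analysis. The downsides are slightly wider intervals and a group variance that may well be estimated at zero, in which case the fitted standard error will be close to the one from the present model. The report should say that such a result does not show that clustering is absent.
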